### Outcome Measures

The primary outcome will be whether or not a patient reaches his/her optimal insulin glargine dose within 12 weeks of enrolling in the study. Optimal insulin glargine dose is defined as the dose at which the patient has at least one fasting blood glucose value within the range of 80 to 130 mg/dL inclusive, or the maximum dose that can be safely administered to the patient. The research staff will record whether a patient has reached their optimal insulin dose at the time of the patient’s weekly titration phone call (if in the MITI arm) or clinic appointment (if in the usual-care arm).

We hypothesize that the MITI arm will have a greater proportion of patients who reach their optimal insulin dose than the usual-care arm. Other clinical effectiveness outcomes include the time taken to reach optimal dose, the incidence of hypoglycemia, and the change in HbA1c levels between baseline and 3 months.

Feasibility measures include patients’ text message response rate, ability of the diabetes nurse educator to reach patients for insulin titration, and the time spent by the diabetes nurse educator on the intervention.

We will measure patient treatment satisfaction at baseline and 3 months after study enrollment using the Diabetes Treatment Satisfaction Questionnaire. We will use an additional questionnaire—the “change” version of the Diabetes Treatment Satisfaction Questionnaire—to measure the change in the patient’s treatment satisfaction between baseline and 3 months [20]. We will also use a semistructured interview to gather qualitative feedback from patients in the MITI arm. This will be administered when the patient has completed the intervention—by reaching their optimal insulin dose or when 12 weeks elapse.  

We will collect data on the costs of insulin titration to compare the intervention to the established standard of care in the clinic. These outcomes include the time spent by patients traveling to the clinic, time spent in the waiting room prior to appointments, number and duration of insulin titration appointments, patient co-pays, and patient health care utilization (ie, the number of noninsulin-related medical clinic visits made at Bellevue during the 12-week study period).

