### Interventions

#### Usual-Care

Patients in the usual-care arm will continue with the treatment plan and appointments decided upon with their clinician prior to enrolling in the study (see Figure 1). According to the clinic’s current practice, a clinician reviews the patient’s fasting blood glucose log during appointments and titrates the insulin dose. Our research assistant (RA) will collect data, such as fasting blood glucose readings, insulin dosage adjustments, and appointment duration, from patients after appointments, in-person or by phone, as well as appointment duration from clinicians. These patients will continue to visit their primary care providers and have routine HbA1c tests according to the standard of care.

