#### Mobile Insulin Titration Intervention

Patients in the MITI arm will sign up for a Web-based health management platform in the clinic with the assistance of the research staff. The platform allows patients and clinicians to communicate via text messaging. Patients will receive a text message each weekday from the platform requesting the patient’ s fasting blood glucose level for that day. The messages will be automatically delivered each morning at a time prespecified by the patient, in either English or Spanish. Patients will respond via text message with their fasting blood glucose levels. Mobile phones can be provided to any patient who is otherwise eligible but does not have a mobile phone. It is implicit that a patient must be able to operate a mobile phone to participate in the study.

The diabetes nurse educator will check patients’ responses on the secure Web portal each weekday and call any patient reporting alarm values (ie, a blood glucose level <80 mg/dL or >400 mg/dL). Each Thursday afternoon, the diabetes nurse educator will call the patients to adjust their insulin dose according to a titration algorithm developed by physicians and nurses on the study team. The diabetes nurse educator may leave a voicemail with insulin titration instructions. If the patient cannot be contacted by phone, the diabetes nurse educator may call the patient’s emergency contact upon her discretion. Another clinician may check text responses and make titration phone calls if the diabetes nurse educator is not available. If Thursday is a holiday, the titration calls can take place on another weekday.

This protocol of weekday text messages and weekly phone calls will continue for up to 12 weeks (see Figure 2), until the patient reaches their optimal insulin dose, or the patient chooses to withdraw from the study. Patients may attend appointments with their primary care provider during the intervention, but will not need to attend appointments specifically for diabetes management (eg, high HbA1c clinic or diabetes nurse educator appointments) within the primary care clinic. After completing the protocol, the patient will be transferred back to usual care in the clinic. The research team will arrange for follow-up appointments with the patient’s primary care provider and, if appropriate, appointments with the diabetes nurse educator or high HbA1c clinic, so that the patient can resume their diabetes care through standard clinic visits.

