### Data Analysis

First, we will summarize all the baseline and follow-up measures using means and standard deviation (SD), medians and interquartile range (IQR), or frequencies, and then compare them between the two arms. Second, we will test if baseline characteristics (eg, demographic measures and baseline HbA1c levels) are balanced between the two randomized arms. Third, to evaluate the intervention effects, we will use the chi-square test or Fisher’s exact test for categorical outcomes (eg, whether or not a patient reaches optimal dose), Student’s *t* test or Wilcoxon rank-sum test for continuous outcomes (eg, change in HbA1c levels, rate of hypoglycemia, scores on the Diabetes Treatment Satisfaction Questionnaire, number and duration of titration appointments, and patient health care utilization), and log-rank test for time to reach optimal dose. Fourth, we will conduct multiple linear regression analyses for continuous outcomes and multiple logistic regression analyses for categorical outcomes to further evaluate the intervention effects, adjusting for some baseline characteristics and/or their interactions with the treatment assignment. At this stage, we will conduct multiple imputation to deal with the missing data problem. Finally, we will conduct descriptive analyses for other secondary outcomes, such as feasibility outcomes, patient travel time and waiting room time, and patient co-pays. We will also review the content of semistructured interviews to identify common themes in patient feedback.

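### Time to optimal dose is tested by an ordinary log-rank test while attainment is recorded weekly in MITI but only at appointments in usual care; if contact dates are used, part of any usual-care lag is detection delay

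*Protocol article*

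**What the plan says.** All references are to the protocol article.

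- **Outcome.** Outcome Measures puts it among the secondary effectiveness measures: "Other clinical effectiveness outcomes include the time taken to reach optimal dose". The primary outcome is binary: "whether or not a patient reaches his/her optimal insulin glargine dose within 12 weeks of enrolling in the study".
- **Event.** There are two routes. One is "at least one fasting blood glucose value within the range of 80 to 130 mg/dL inclusive"; the other is arrival at the highest dose that is safe for the patient.
- **Recording.** Staff note attainment at the "weekly titration phone call (if in the MITI arm) or clinic appointment (if in the usual-care arm").
- **Contact schedule.** In MITI: "Each Thursday afternoon, the diabetes nurse educator will call the patients to adjust their insulin dose". In usual care no interval is given: "Patients in the usual-care arm will continue with the treatment plan and appointments decided upon with their clinician prior to enrolling".
- **Readings available.** MITI patients text fasting values each weekday. For usual care, the Usual-Care section says that the research assistant "will collect data, such as fasting blood glucose readings, insulin dosage adjustments, and appointment duration, from patients after appointments", in person or by phone.
- **Test.** Data Analysis names a "log-rank test for time to reach optimal dose" and makes no allowance for unequal assessment. The limitations in the Discussion cover sample size, volunteer bias, lack of blinding and observer bias, but not this.

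**The concern.** The glucose route happens at home on a particular day, but the recording rule ties it to the next contact. That contact is at most about a week away in MITI and as far off as the next appointment in usual care. Contact-dated times are interval-censored, with wider intervals in one arm, and an ordinary log-rank test takes each recorded date as exact. Two arms with the same true course would then give a later usual-care curve, in the direction of the trial's hypothesis. Events that fall between a usual-care patient's last appointment and week 12 would not be recorded at all. At stake is a secondary result that could be read as faster titration when some of it is faster recording.

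**Working it through.** **1. The plan's own figure.** The only design calculation is for the binary primary outcome: 80% v 50%, Fisher's exact test, two-sided 5%. Exact power is 79.6% at 43 per group and 80.2% at 44, so 44 is reproduced. Then 44/0.9 = 48.9, rounded up to 49 per group, 98 in total. This point leaves that figure unchanged. No figure is given for the log-rank test.

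**2. Inputs for the check.**
- From the article: 44 per arm, a 12-week window, weekly recording in MITI, and at most 50% reaching the dose in usual care (Sample Size).
- Assumed: usual-care visits every k = 2, 4 or 6 weeks; exponential true times, the same in both arms; events dated at the contact; patients with no recorded event censored at week 12.

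**3. Formulas.** If a proportion p reaches the dose by week 12, the weekly hazard is λ = −ln(1−p)/12. For p = 0.50, 0.65 and 0.80 this is 0.058, 0.087 and 0.134. The MITI time is rounded up to the whole week. The usual-care time is rounded up to the next visit, either on fixed days (k, 2k, ...) or staggered, with the first visit uniform on 0 to k. The log-rank test rejects at |z| > 1.96.

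**4. Delay.** The mean recording delay in usual care with staggered visits is about 1.0, 1.9 and 2.8 weeks for k = 2, 4 and 6. Weekly recording costs about half a week in MITI, so the net delays are about 0.5, 1.4 and 2.3 weeks.

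**5. Two-sided rejection with no true difference** (2,000 trials per cell; Monte Carlo standard error √(0.05×0.95/2000) ≈ 0.5 points near 5%, about 1 point for the larger rates):

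| Reaching dose by week 12 | k = 1 | k = 2, fixed / staggered | k = 4, fixed / staggered | k = 6, fixed / staggered |
|---|---|---|---|---|
| 50% | 4.4% | 5.3% / 5.0% | 7.0% / 9.7% | 11.0% / 19.9% |
| 65% | 5.3% | 5.3% / 7.2% | 11.4% / 12.9% | 26.6% / 26.7% |
| 80% | 5.0% | 7.5% / 7.0% | 28.0% / 19.0% | 63.0% / 41.2% |

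With weekly recording in both arms the test holds its level. At k = 4 and 6 nearly all rejections favour MITI. In the 50% row, repeat runs of the same model span about 5-7% (k = 2), 7-13% (k = 4) and 9-21% (k = 6). With staggered visits, a true 50% in usual care is recorded as 46.9%, 43.8% and 40.2%, because late events are missed.

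**6. Dependence on the censoring date.** I reran the model with 10,000 trials per cell. Week-12 censoring gave the same pattern (50% row, fixed / staggered: 5.3 / 6.0%, 7.0 / 9.5%, 10.6 / 18.6%). With staggered visits and event-free usual-care patients censored at their last appointment, the 50% row is 5.4%, 5.8% and 5.8%. The inflation largely cancels, although 9.6% remains at 80% with k = 6. The cancellation is accidental: late recording is offset by early removal from the risk set.

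**7. After correction,** over the nine combinations of p and k with staggered visits, rejection is 4.3-6.5% with dating from the log and usual care censored at the last appointment, 4.2-6.2% on a common grid, and 4.2-6.2% with an interval-censored exponential likelihood-ratio test.

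**The case against.** - **The article does not say which date enters the analysis.** Outcome Measures says when attainment is recorded. Clinicians review the glucose log and the research assistant collects usual-care readings, so back-dating is possible, and the derivation rule could sit in an analysis plan that is not shown. This stands in part. Contact dating is the natural reading of the recording rule but is not stated outright, so the point is conditional. It is still more than a missing detail, because the stated recording rule and the stated test, followed as written, combine badly.
- **Slower titration is what usual care is.** The outcome is reaching a dose, doses change at contacts, and MITI's rationale is more frequent titration. The highest-safe-dose route is settled at a contact, so its contact date is arguably its true date. This stands: some of the lag may be real, and the simulation, whose true times do not depend on contact frequency, measures only the detection part.
- **The visit intervals are assumed.** This stands. At 2-weekly visits the effect is close to nothing. The Background does say that these patients struggle to attend often enough for regular titration, which makes near-weekly contact in usual care unlikely.

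A reader might take the largest rates, around 40-60% at 6-weekly visits, as the size of the problem. The article does not support that. Those rates need 80% of both arms to reach the dose, against at most 50% expected in usual care. The top value also needs every usual-care patient to be seen on the same days, whereas appointments are arranged individually.

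**Conclusion.** The point holds in conditional form and should be fixed before analysis. If contact dates are used, the ordinary log-rank test mixes detection delay with any true difference, in MITI's favour, and cannot separate them. At the 50% usual-care rate in Sample Size, the two-sided false-positive rate is about 5-7%, 7-13% and 9-21% for assumed 2-, 4- and 6-weekly visits, and it rises if more patients reach the dose.

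These figures rest on exponential times and on censoring at week 12. Week 12 is the natural end of the stated window, but no censoring rule is given, and censoring staggered usual-care patients at their last appointment would remove most of the inflation.

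Two stronger inferences are not supported. This is not a headline result: it is a secondary outcome in a study that calls itself a pilot, and the sample size is unaffected. Nor is a later usual-care curve wholly an artefact, since less frequent titration may truly delay the dose.

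**What to change.** - **Glucose route.** In both arms, date the event by the calendar day of the first qualifying fasting reading: the texts in MITI, and the readings that the research assistant already collects in usual care. Count the same days of the week in both arms, since MITI texts are weekday-only while usual-care logs are daily. Censor at the last date with readings.
- **Highest-safe-dose route.** Keep the contact date.
- **Where only contact dates exist.** Treat the time as lying between the last contact without the event and the first contact with it, and use an interval-censored test. Alternatively, compare both arms on a common grid, using only points at which status is known in both.
- **Reporting.** State the dating and censoring rules, and report contact frequency by arm so that readers can judge how much of any lag could be recognition and how much titration.

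The cost is one extra date field, minor programming and slightly less precision. The article says that data were still being collected, so the rule can be set before the analysis.

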### Implementation Challenges

During this pilot study, we refined our technological approach because our initial health management platform could not send text messages to prepaid mobile phones. Patients who had prepaid mobile phones either continued to attend in-person clinic appointments for insulin titration or were provided a mobile phone to use for the duration of the study. We resolved this issue in 2014 when we switched to a different health management platform that could send text messages to any mobile phone.

Prior to May 2014, patients were stratified by whether the patient was initiating insulin therapy or having their existing insulin dose titrated, and by HbA1c level (8-11% or >11%). We removed the HbA1c stratification after finding that not all patients had an HbA1c value available in their medical record at the time of enrollment.

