### Recruitment, Randomization, and Retention

We will recruit patients from the Adult Primary Care Center. Clinicians can alert the research study staff of any patient who is interested in the study and may be eligible (see Figure 3). The RA will also review the clinic’s electronic medical records to identify patients that may be eligible for the study. The RA will screen the patient for eligibility, explain the study, and provide them with a consent form to read and sign in person at the Adult Primary Care Center. All patients must provide informed consent before participating in the study protocol.

Since patients will be randomized sequentially at the time they provide informed consent, we will use block randomization (block size of 4) to make sure the number of patients in each arm is approximately balanced at any time point during the study. Patients will be stratified by whether the patient is initiating insulin therapy or having their existing insulin dose titrated. The random allocation sequence will be computer-generated by a coinvestigator and concealed in presealed envelopes. The patient’s arm assignment will be revealed to the patient and research team at the time of study enrollment by the RA. The research team and clinicians will not be blinded since the intervention requires that they alter the patient’s treatment plan or, in the case of the usual-care arm, collect data from clinicians and patients regarding their appointments.

At the time of enrollment, patients will receive a US $10 MetroCard to be used for travel to and from the clinic. Patients will receive a glucometer and a supply of test strips to ensure that they can test their blood glucose levels for the duration of the study. At approximately 12 weeks into the study, the research assistant will contact patients by phone to remind them to return to the clinic for their 3-month HbA1c blood test and complete the satisfaction questionnaire. Patients will receive an additional US $10 MetroCard.

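### The log-rank test for time to optimal dose (a secondary outcome) names no strata and has no survival model beside it, so it gives up power to the extent that the randomisation stratum is prognostic

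*Protocol article*

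**What the plan says.** **Randomisation.** The section on recruitment and randomisation uses blocks of 4 and states: "Patients will be stratified by whether the patient is initiating insulin therapy or having their existing insulin dose titrated". Implementation Challenges shows that the same factor was in use earlier: "Prior to May 2014, patients were stratified by whether the patient was initiating insulin therapy or having their existing insulin dose titrated", alongside HbA1c in two bands. Only the second factor was dropped: "We removed the HbA1c stratification after finding that not all patients had an HbA1c value available". Starting versus existing insulin is therefore the one factor behind every allocation in the trial.

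**Analysis.** The Data Analysis section assigns tests by type of outcome. Categorical outcomes get a chi-square or Fisher test, continuous outcomes a t test or rank-sum test, and the time outcome a "log-rank test for time to reach optimal dose". The next step adds "multiple linear regression analyses for continuous outcomes and multiple logistic regression analyses for categorical outcomes", "adjusting for some baseline characteristics and/or their interactions with the treatment assignment". No model is listed for the time outcome, and the stratification factor is not named anywhere in the section.

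**Status of the outcome.** Outcome Measures lists time to optimal dose among the other clinical effectiveness outcomes, directly after the primary hypothesis. It is secondary.

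**The concern.** Stratified blocks force the two insulin groups to be nearly balanced between arms. If the groups reach their optimal dose at different speeds, that balance removes a source of chance difference between arms. A log-rank test that ignores the strata still counts this source in its variance. It also pools patients with different hazards, which dilutes the treatment effect. Its true type I error then falls below 5%, and power falls with it.

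A second gap goes with this. The article takes each of the other two outcome types on to a model that yields an adjusted effect. The time outcome stops at a test, so no relative effect with a confidence interval is described for it. The Discussion itself warns that a small sample will limit power, so information already collected at randomisation is worth using.

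**Working it through.** **1. The plan's own figure.** No sample size or power is stated for the log-rank comparison. The stated size is for the primary binary outcome: 50% versus 80%, two-sided 5%, Fisher's exact test. Exact enumeration gives power of 79.6% at 43 per group and 80.2% at 44, so 44 is reproduced. Allowing for drop-out, 44 / 0.9 = 48.9, so 49 per group and 98 in total, as stated.

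**2. Treatment effect on the time scale.** Under proportional hazards, 50% and 80% attainment at 12 weeks imply HR = ln(1 − 0.80) / ln(1 − 0.50) = 2.32. A smaller effect, HR 1.8, corresponds to 1 − 0.5^1.8 = 71% versus 50%.

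**3. Simulation.**
- *From the article:* 98 patients, 1:1 allocation in blocks of 4 within two strata, 12 weeks of follow-up, 10% drop-out, 50% usual-care attainment.
- *Assumed, because the article does not give them:* the stratum hazard ratio (1 to 5), the stratum mix (50:50, then 25:75), exponential times read weekly in both arms, and drop-out spread evenly over the 12 weeks.
- *Runs:* 10,000 trials per cell, both tests at two-sided 5%.

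Results with 50:50 strata, plain / stratified, in %:

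| Stratum HR | Type I error | Power, HR 2.32 | Power, HR 1.8 |
|---|---|---|---|
| 1 | 4.7 / 4.7 | 91.2 / 90.9 | 59.8 / 59.3 |
| 1.5 | 4.7 / 4.8 | 90.3 / 90.6 | 58.4 / 59.1 |
| 2 | 4.6 / 5.3 | 88.1 / 90.1 | 55.9 / 59.6 |
| 3 | 3.5 / 4.9 | 83.9 / 89.4 | 50.3 / 59.4 |
| 5 | 2.4 / 5.2 | 71.7 / 88.1 | 39.0 / 57.8 |

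Monte Carlo error is about 0.2 points for type I error and 0.3 to 0.5 points for power. With 25% of patients in the faster stratum, power at HR 2.32 is 89.1 / 90.5 at a stratum HR of 2, 84.6 / 89.2 at 3 and 75.9 / 88.2 at 5. Plain type I error is then 3.9% at 3 and 2.4% at 5.

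**4. What the assumed stratum effects mean.** Let x be the usual-care probability of not having reached the optimal dose by week 12 in the slower stratum, and θ the stratum HR. With equal strata and 50% overall, 0.5(x + x^θ) = 0.5.
- θ = 2: x = 0.618, so attainment is 38% versus 62% in the two strata.
- θ = 3: x = 0.682, so 32% versus 68%.
- θ = 5: x = 0.755, so 25% versus 75%.

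**5. A caution on the table.** It holds the within-stratum treatment HR at 2.32, so overall MITI attainment is exactly 80% only when θ = 1. In general it is 1 − 0.5(x^2.32 + x^(2.32θ)), which gives 78% at θ = 2, 76% at 3 and 72% at 5. Part of the fall down the plain column reflects this. The gap between the two tests within a row is the relevant figure.

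Holding overall attainment fixed instead (44 per arm, half starting insulin, 2,000 runs, stratum HR 3) gives 94% versus 97% for 80% versus 50% attainment, and 54% versus 64% for 70% versus 50%. The plain test's size is then 3.0%, against 5.3% for the stratified test. The direction is the same, and the gap at the planned effect is smaller.

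**The case against.** **The strata are missing only by silence.** The article never says that the test is unstratified, and a statistical analysis plan that is not shown could add strata or a Cox model. A reader might infer that the trial will certainly ignore its strata; the article does not support that. What stands is narrower. The article sets out its analyses by outcome type, names a specific test for this one, and lists adjusted models that leave it out. A better method than the stated one is available without new data.

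**The loss is conditional.** A reader might infer that the plain test simply is conservative and underpowered. The article does not support that either. It gives no stratum effect and no mix. All patients enter with raised HbA1c, and the endpoint can be met by a single in-range fasting value, so the two groups may differ little. At stratum hazard ratios of 1 to 1.5 the loss is under one point. This objection is accepted in full.

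**The large gaps come from scenarios outside the plan.** Stratum hazard ratios of 3 and 5 and an effect of 70% versus 50% are assumptions. Weekly reading also simplifies the usual-care arm, where attainment is recorded at clinic appointments. Both points are accepted. The figures show a range and are not an expected loss.

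**Validity is not at risk.** This is a secondary outcome in a self-described pilot, and the error is on the conservative side. That is correct.

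**Some description is planned.** The first analysis step summarises all follow-up measures by arm, so it would be too strong to say that the time outcome gets nothing but a p-value. What is missing is a relative effect with a confidence interval.

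None of this counts against stratifying. If the factor is not prognostic, the cost is within simulation error (91.2% versus 90.9%).

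**Conclusion.** The point holds in conditional form. As written, the analysis of time to optimal dose does not carry the one factor that stratified every allocation, and no survival model accompanies the test. To the extent that starting versus existing insulin predicts time to optimal dose, the test is conservative and loses power.

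At a treatment hazard ratio of 2.32, the loss against the stratified test is nil at a stratum hazard ratio of 1, about 1.5 to 2 points at 2, about 4.5 to 5.5 points at 3, and 12 to 16 points at 5. Type I error falls clearly only from about 3 upwards (3.5 to 3.9% at 3, 2.4% at 5). These sizes rest on assumed stratum strength and mix, exponential times and weekly reading.

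It would be wrong to infer that false positives are inflated, or that the primary comparison or the 98 patients are in doubt. This is an inexpensive gain in efficiency on a secondary outcome.

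**What to change.** In the Data Analysis section, replace the plain test with a log-rank test stratified by starting versus existing insulin. In the adjusted step, add a Cox model stratified by the same factor and report the hazard ratio with its 95% CI.

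This costs a sentence. The stratum is known for every patient because allocation used it, and the article describes follow-up as still under way with results to come, so the change can be fixed before the analysis.

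Baseline HbA1c should be an optional covariate only. Implementation Challenges says that some patients had no value on record at enrolment, so it is not free. If it is used, missing values should go through the multiple imputation already planned.
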